**Fig. 1 Fig1:**
[figure not shown]
Sagittal CT scan of scaphoid non-union. The measurement of dorsal cortical angle (DCA) and height-length ratio (HLR). The height-length ratio is calculated by dividing the scaphoid height by length

Surgical treatment of scaphoid delayed/non-union is technically demanding and often results in a long period with a supportive bandage until union is established. Current treatment strategies for delayed union and non-union include vascularized or non-vascularized bone graft with internal fixation. Kirchner wires or screws have been the gold standard for fixation. A meta-analysis found an average of 94% union with screw fixation and 77% with K-wire fixation in unstable non-union [12]. Open CC graft reconstruction is often preferred [13, 14]. However, there is an increased donor site morbidity from the iliac crest, and the outcome is not superior to distal radius C graft [15]. Arthroscopic reconstruction with C chips and internal fixation is predominantly applied in delayed union and stable non-union [16–18]. The advantages of arthroscopy include thorough wrist assessment, evaluation of concomitant ligamentous injury and minimal trauma to the ligament structures, joint capsule and the tenuous blood supply [19]. Recent studies have reported an 86–100% union rate, also in patients with cystic changes and/or translation > 2 mm, and/or humpback deformity [20–24]. A retrospective study, with 62 cases, found union in 96% arthroscopic group vs. 97% in open surgery with no difference in the functional results, however, time to union was not recorded [16]. No RCT comparing arthroscopic or conventional open C graft technique have been performed.

The objective of this study protocol is to describe the methodology for a randomized controlled trial comparing time to union and functional outcome scores of arthroscopic assisted C chips reconstruction or open C graft reconstruction for scaphoid delayed/non-union. The standard protocol items recommendations for interventional trials (SPIRIT) statement 2013 have been followed for the completion of this protocol (Additional file 1) and the items from the WHO trial registry are found in within the protocol.

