### Outcome measures

#### Primary outcome

Time to union will be assessed with repeated CT scans in 2 weeks intervals from 6 to 16 weeks postoperative. If union is not achieved within 16 weeks, a CT scan will be made 24 weeks postoperatively. If union is not achieved at that point, the patient will be presented for another treatment modality. Union will be proclaimed and recorded when > 50% bone bridging occurs on CT scan [26, 27]. The Minimal clinically important differences (MCID) have not been defined. We use an arbitrary value of 3 weeks difference.

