**Fig. 3 Fig3:**
[figure not shown]
Consort flow diagram. Flow of patient through the study

Patients drop-out/loss to follow-up will be recorded and the reason will be noted. The patient is included in the analysis with their latest follow-up if at least a 6-week evaluation is available. Patients who undergo revision/secondary surgery will remain in the study and will be followed according to the index procedure. Their results before and after the revision procedure are included in the analysis. If challenges in the trial conduct occur, they will be presented by the primary investigator every second week to the research group. Any protocol modifications will be communicated to all investigators, observers and trial registries immediately. No regular audit is planned, apart from possible independent inspection visits by the Data Protection Agency and the National Committee on Health Research Ethics.

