#### Data analysis

Interim data analysis will not be carried out. Continuous data will be presented as means with SD or as median with interquartile range (IQR) depending on the nature of data. Categorical data will be presented as counts with percentages. Differences in demographic data and outcome measures between groups will be compared using chi-square for categorical data and Student’s *t*-test (parametric data) or Wilcoxon signed rank test (non-parametric data) for continuous data.

An intention-to-treat analysis will be conducted for the primary outcome. A per-protocol analysis will be conducted to test the non-adherence to the protocol, and patients who do not comply with the protocol will be excluded. Primary outcome will be analysed with a mixed effect model adjusted for fracture location, smoking habits and dislocation (the strata in the block randomization) to account for imbalance in baseline covariates and to improve the power of the treatment effect.

Subgroup analyses for the duration of non-union (< 6 months vs. > 6 months), patients with/without deformity based on the preoperative measurements of HLR and DCA will be performed. It will be clarified if post hoc analyses are carried out. For missing data in an outcome measure, multiple imputation analysis with the covariates: age, smoking, fracture location, dislocation > / < mm and duration of non-union will be conducted to minimize bias of nonresponse. Applied level of significance for all statistical analyses is *P* < 0.05. The statistical analyses will be performed using computerized statistical software.

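### The primary model and its mean-difference target do not fit one interval-censored union time per patient, and patients ununited at 24 weeks have no stated place in it

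*Protocol article*

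**What the plan says.** All references are to the protocol article.

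- **Outcome (Primary outcome).** The main schedule is: "Time to union will be assessed with repeated CT scans in 2 weeks intervals from 6 to 16 weeks postoperative". One later scan is foreseen for those who have not healed by the end of that schedule: "If union is not achieved within 16 weeks, a CT scan will be made 24 weeks postoperatively". The event is defined by "Union will be proclaimed and recorded when > 50% bone bridging occurs on CT scan". For patients still ununited at 24 weeks: "If union is not achieved at that point, the patient will be presented for another treatment modality".
- **Target (Hypothesis; Sample size calculation).** A mean difference of 3 weeks, planned with 56 days (SD 30) in the arthroscopic arm and 77 days (SD 40) in the open arm.
- **Model (Data analysis).** "Primary outcome will be analysed with a mixed effect model adjusted for fracture location, smoking habits and dislocation". No random effect, outcome scale or censoring rule is given. The other tests named are chi-square, t and Wilcoxon tests. No time-to-event method appears anywhere.
- **Incomplete or altered follow-up (Protocol violations and patient drop-out).** Drop-outs enter with their last available follow-up if they were seen at 6 weeks or later. For revised patients: "Their results before and after the revision procedure are included in the analysis".
- **Missing data (Data analysis).** Multiple imputation, with the stated purpose of reducing nonresponse bias.
- **How often union fails (Background).** For arthroscopic series: "Recent studies have reported an 86–100% union rate". One retrospective comparison of 62 cases found 96% union with arthroscopy and 97% with open surgery.

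**The concern.** A healing time read from this CT schedule is interval-censored. It lies before 6 weeks, in a 2-week window up to 16 weeks, or in the 8-week window from 16 to 24 weeks. A patient ununited at 24 weeks is right-censored and has no value that can enter a mean.

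A linear model for days to union has three ways to treat such a patient: leave the patient out, enter a chosen number of days, or enter the day of last follow-up as if union had occurred then. Leaving the patient out conditions on healing, which is an outcome of treatment, so the comparison is no longer by intention to treat. The last-follow-up rule, applied to an ununited drop-out, turns a censoring time into a union time. The article does not say which applies to the primary outcome, so the choice could be made after the data are seen. If non-union differs between arms, that choice can change the answer materially.

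With one time per patient and no cluster named, the random effect also has no stated role.

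**Working it through.** **1. The plan's own figure.** Inputs: difference 21 days, SDs 30 and 40, 80% power, two-sided 0.05. The number per arm is (1.960 + 0.842)² × (30² + 40²) / 21² = 7.85 × 2500 / 441 = 44.5, so 45. The stated 36 is matched only by a one-sided 0.05 test: (1.645 + 0.842)² × 2500 / 441 = 35.1, so 36. Two-sided power at 36 per arm is about 71%. This is a separate matter, but it is the baseline for the power figures under the fix.

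**2. How much is censored.** Shares from the planning means and SDs under normal, lognormal and gamma shapes (the article states no shape):

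| | Arthroscopic | Open |
|---|---|---|
| United before day 42 (first CT) | 32–37% | 16–19% |
| Not united by day 112 (16 weeks) | 3–5% | 16–19% |

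Example, normal: (42 − 56)/30 = −0.47 gives 32%; (42 − 77)/40 = −0.875 gives 19%.

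**3. Recorded times on the CT grid.** Assume lognormal times with σ² = ln(1 + (SD/mean)²) and μ = ln(mean) − σ²/2. This gives μ = 3.899, σ = 0.502 (arthroscopic) and μ = 4.224, σ = 0.489 (open). Union is recorded at the first of days 42, 56, 70, 84, 98, 112 and 168 on or after it occurs. The shares at those days are:

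- arthroscopic: 0.374, 0.225, 0.157, 0.098, 0.059, 0.035, 0.044 (sum 0.993);
- open: 0.160, 0.182, 0.178, 0.144, 0.106, 0.074, 0.123 (sum 0.967).

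The mean recorded time among the united is 65.1 days (arthroscopic) and 83.6 days (open). The difference is 18.5 days whatever share never unites, because that share cancels when non-unions are dropped.

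**4. Counting non-unions at 24 weeks (168 days).** With never-united share p, the share united by 24 weeks is U = (1 − p) × 0.993 (arthroscopic) or (1 − p) × 0.967 (open). The arm mean is U × (mean among united) + (1 − U) × 168.

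- p = 4% and 3%: arthroscopic 0.953 × 65.1 + 0.047 × 168 = 70.0; open 0.938 × 83.6 + 0.062 × 168 = 88.8; difference **18.8 days**.
- p = 14% and 6%: arthroscopic 0.854 × 65.1 + 0.146 × 168 = 80.2; open 0.909 × 83.6 + 0.091 × 168 = 91.3; difference **11.1 days**.
- p = 6% and 14%: the same formula gives **25.8 days**.

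If 4% and 3% are instead the whole share open at 24 weeks, the means are 0.96 × 65.1 + 0.04 × 168 = 69.3 and 0.97 × 83.6 + 0.03 × 168 = 86.1. The difference is then 16.9 days, still a small shift.

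**5. Another arbitrary value.** Scoring non-unions at 1 year gives about 21.7 days (4%/3%), 0 days (14%/6%) and 45.7 days (6%/14%).

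**The case against.** Several objections are sound and limit the point.

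- **The wording does not rule out a suitable model.** A reader might infer that a mixed effect model cannot handle this outcome. That is true only of a linear model on one time per patient. Up to seven CT readings per patient are repeated union-status data, and a discrete-time mixed model on them would fit the wording. Surgeon could be a cluster. The article says neither, and its mean-difference target points to the linear reading.
- **Imputation.** A reader might infer that a never-united patient would be given an imputed healing time. The stated purpose is nonresponse. A patient scanned at 24 weeks and seen not to be united has responded, so the document does not support that inference. It also does not exclude it.
- **Revision.** A reader might infer that union after a second operation would be credited to the index arm. The scheduled route to further treatment opens only after the 24-week CT, the last scan for this outcome. Crediting would need an earlier revision or extra scans, and the revision rule covers all outcomes.
- **A hidden union difference.** Union rate is a separate CT-based secondary outcome, so a difference would be reported. The primary estimate would still not reflect it.
- **Size.** At 14% against 3% never uniting and equal healing speed, dropping gives 0 days and counting at 24 weeks about 10, near half the planned 21. That is a stress case: it pairs the worst arthroscopic series with the open arm of another study. The only comparative rates in the document, 96% and 97%, make the choice matter little.
- **Deferred detail.** A scoring rule might sit in an unseen analysis plan. But the article itself names the model and the target, so a suitable plan would have to replace or reinterpret them.

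**Conclusion.** The point holds in limited form. The article assigns a model and a mean-difference target to a single interval-censored time that is undefined for patients ununited at 24 weeks, and its general follow-up rules do not settle how those patients enter. It does not show that every mixed model would fail, or that the result will be badly distorted.

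If non-union is rare and balanced, as in the one cited comparison, the scoring choice moves the difference by about half a day (18.5 against 18.8), or by about 1.6 days on the other reading of those rates. If the arms differ, at 14% and 6%, the difference is 18.5 or 11.1 days depending on the choice. These figures rest on the planning means and SDs, a lognormal shape and assumed never-united shares. The balance between arms cannot be known in advance, so the rule should be fixed before the data are seen.

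**What to change.** 1. **Model.** State the primary analysis as an interval-censored time-to-event regression, or a discrete-time complementary log-log regression over the seven CT visits, with arm and the three randomisation strata.
2. **Who counts as what.** Keep patients ununited at 24 weeks as not united by the index procedure. Censor drop-outs at their last CT. State that neither multiple imputation nor results after a revision supply a union time for the primary outcome.
3. **Estimand.** Name one. The difference in restricted mean time to union to 24 weeks, with 95% CI, keeps the 3-week target readable; the hazard ratio can be supportive. With complete follow-up the restricted mean counts a non-union as 24 weeks. It therefore adopts one of the scorings above, deliberately and in advance, and the text should say so. It should also say whether union is placed at the detecting CT or within the interval, because recording at the CT alone moves the planned 21 days to about 18.5.

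**Cost.** No new data and standard software, but the primary test and estimand change, so power must be restated. In simulations at 36 per arm with the planning inputs and lognormal times:

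| Never united (arthroscopic/open) | Non-unions dropped, t-test | Log-rank, censored at 24 weeks |
|---|---|---|
| 0%/0% | 62% | 69% |
| 4%/3% | 60% | 49% |
| 6%/6% | about 58% | about 46% |

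A mean comparison counting non-unions at 24 weeks, close to a restricted-mean test with complete follow-up, had 53% power at 4%/3%. The higher power from dropping non-unions answers a different question, about healed patients only. The stated 80% should be recalculated for the chosen analysis.

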### Statistics

#### Sample size calculation

The sample size calculation was performed with an expected mean time to union of 56 days and a SD of 30 days in Group A and 77 days and SD on 40 days in group B. The sample size required in each group to provide 80% power to detect a mean 3 weeks difference [13], with two-sided alpha on 0.05, was 36 patients in each group. Considering dropouts and loss to follow-up with a rate of 20% the final number of patients needed in total for this study is 88 patients.

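### The printed list of multiple-imputation covariates leaves out treatment arm, so imputing as written shrinks the treatment difference by about the share imputed

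*Protocol article*

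**What the plan says.** The imputation rule stands in the Data analysis section of the protocol article. It covers every outcome: "For missing data in an outcome measure, multiple imputation analysis" is to be used. The list of covariates opens with "multiple imputation analysis with the covariates: age, smoking, fracture location", continues with dislocation, and closes with "and duration of non-union will be conducted to minimize bias of nonresponse". All five are baseline characteristics, and three of them (smoking, fracture location, dislocation) are the randomisation strata. The list contains neither treatment arm nor any value of the outcome itself, and imputation within arm is not mentioned.

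The same section describes the main analysis: "Primary outcome will be analysed with a mixed effect model adjusted for fracture location, smoking habits and dislocation", with the aim of estimating a treatment effect.

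The Enrolment section shows that Q-DASH, pain, range of motion, grip and key pinch are recorded at baseline. The Follow-up section schedules clinical and patient-reported outcomes at 1.5, 3, 6, 12 and 24 months. Values that could inform the imputation are therefore collected.

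**The concern.** An imputation model should contain every term that the analysis model estimates. Here the analysis estimates a difference between arms, while the imputation model, taken literally, sets that difference to zero for every imputed value. Two patients with the same five covariates but different operations get draws from the same distribution. Mixing those draws with the observed data pulls the estimated difference toward zero.

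This happens even if data are missing completely at random. An analysis of the observed patients alone would then be unbiased, so a step meant to reduce non-response bias would introduce one. The rule applies to any outcome measure, so Q-DASH and donor-site pain are affected as well as time to union. For a comparison in which a real difference between arms is expected, shrinkage favours a finding of no difference.

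**Working it through.** The plan gives no figure for the imputation, so there is none to reproduce. The inputs come from its Sample size calculation section.

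**Inputs**
- Arthroscopic group: "expected mean time to union of 56 days and a SD of 30 days in Group A".
- Open group, there called group B: "77 days and SD on 40 days in group B".
- Target: "to provide 80% power to detect a mean 3 weeks difference", that is 77 − 56 = 21 days.
- 44 patients per arm (Subjects and Randomization sections).
- Dropout allowance: "Considering dropouts and loss to follow-up with a rate of 20" per cent.

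A side note on the plan's 36 per group. The two-sided formula gives (1.960 + 0.842)² × (30² + 40²) / 21² = 44.5, so 45. One-sided alpha of 0.05 gives (1.645 + 0.842)² × 2500 / 441 = 35.1, so 36. That is a separate matter and does not enter the result below. It does explain why power in the simulations starts below 80% even when arm is included.

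**Analytic check.** Let a fraction m be missing in each arm, completely at random. Without arm in the model, imputed values in both arms centre on the common mean (56 + 77)/2 = 66.5 days. At m = 0.20:
- Arthroscopic: 0.8 × 56 + 0.2 × 66.5 = 58.1
- Open: 0.8 × 77 + 0.2 × 66.5 = 74.9
- Difference: 74.9 − 58.1 = 16.8 days

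In general the difference is (1 − m) × 21, giving 19.95 days at 5%, 18.9 at 10%, 16.8 at 20% and 14.7 at 30%.

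**Simulation.** Two simulations were run with 44 per arm and a true difference of 21 days.
- S1: 3000 trials per scenario, 10 imputations, data missing at random, covariates assumed to explain 15% of the variance.
- S2: 1500 trials per scenario, 20 imputations, data missing completely at random, listed covariates without prognostic value, analysis adjusted for arm and the three strata.

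| Share imputed | Analytic, no arm | S1, no arm | S1, with arm | S2, no arm | S2, with arm |
|---|---|---|---|---|---|
| 5% | 19.95 | 20.05 | 20.95 | – | – |
| 10% | 18.9 | 18.92 | 21.10 | 18.60 | 20.80 |
| 20% | 16.8 | 16.77 | 21.08 | 16.59 | 20.98 |
| 30% | 14.7 | – | – | 14.14 | 20.63 |

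In S2 the Monte Carlo error of a mean at 20% is about √(2500/35.2)/√1500 = 8.43/38.7 = 0.2 day. Analysing observed patients only gave 20.93 days at 20% missing in S2, so the shrinkage comes from the imputation and not from the missing data.

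Power without and with arm:
- S1: 72% and 76% at 5%; 65% and 75% at 10%; 49% and 69% at 20%.
- S2: 61% and 70% at 10%; 45% and 67% at 20%.

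**Other measurements.** S2 also added a second measurement with an assumed correlation of about 0.65 with the outcome. At 20% missing:
- Arm, no second measurement: 20.98 days, power 67%.
- Arm and second measurement: 21.00 days, power 71%.
- Second measurement, no arm: 18.68 days, so the bias is only partly repaired.

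The bias therefore comes from omitting arm. Omitting other measurements costs some power.

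**The case against.** The strongest reply is that the list was never meant to be complete. The sentence on the primary model also names only the three strata and not arm, yet that model must contain arm to yield a treatment effect. Read the same way, the imputation list names baseline covariates used alongside arm. This reading is possible. It is not stated, however, and the two sentences differ: a model that estimates a treatment effect contains arm by necessity, whereas an imputation model runs perfectly well without it.

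A second reply is that imputation details belong in an analysis plan that is not shown. That holds for the algorithm, the number of imputations and similar detail. It does not cover a covariate list that the article itself prints.

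Three further points stand and limit the claim:
- The share imputed is unknown. The 20% is a sample-size allowance, and the section on protocol violations and drop-out keeps a patient in the analysis with the latest follow-up once a 6-week evaluation exists. That may leave fewer values to impute, although how the two rules fit together is not stated. At 5% the loss is about one day.
- The article does not say whether imputation feeds the primary estimate or a supporting analysis.
- The bias is toward no difference, so in a superiority trial it would not by itself create a false claim of benefit.

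A reader might also infer that omitting the other visits pulls the effect toward zero. The calculations do not support that once arm is in the model.

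**Conclusion.** The concern holds for the list as printed: imputation pooled across arms and without arm shrinks the treatment difference in proportion to the fraction imputed. The 21-day difference becomes about 20 days at 5%, 18.9 at 10% and 16.8 at 20%. This assumes that the list is complete, that missingness is similar in the two arms, and that imputation supplies the estimate reported.

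A reader might go further and conclude that the primary analysis will lose a fifth of its effect, or that its power will drop to between 45% and 49%. The document does not support that, because those figures apply only if the whole dropout allowance is imputed for the primary outcome. Nor does it show that arm was deliberately left out.

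Omitting baseline and other-visit values is a lesser point. It loses precision (67% against 71% power in the case simulated) and makes missing-at-random harder to defend, because a patient's own earlier and later scores are likely to carry information about a missing one.

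**What to change.** Amend the imputation sentence in the Data analysis section, or settle it in the analysis plan before the data are analysed:
- Include treatment arm in the imputation model, or impute separately by arm.
- Keep the five listed covariates; they already include the three randomisation strata.
- Add the baseline and other-visit values of the same outcome where these are collected.

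It would help to say in the same place how the latest-follow-up rule and the imputation fit together, so that the values to be imputed are defined.

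The cost is a sentence or two of text. Every variable needed is already collected, and neither sample size nor visits change.
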